## Introduction

### Background and rationale

Institute for Safe Medication Practices (ISMP) data suggest that approximately 300,000 Canadians suffer serious, disabling, or fatal medication-related harm annually [1, 2]. Anticoagulants are the most common cause of medication-related serious harm, in terms of emergency department visits, hospitalizations, and fatalities [3, 4]. Transitions in care have been identified as a particularly high-risk period for adverse events [5]. Each adverse drug event requiring a hospital visit approximately doubles the cost of care in the subsequent 6 months [1]. Indeed, our previous study of thromboembolic and hemorrhagic events after hospital discharge for patients taking oral anticoagulants (OACs) found rates to be approximately 2 to 3 times higher in the first month compared to later [6]. Root cause analyses and patient safety inquiries cite problems with recognition of individual risk factors for benefit versus harm, drug interactions and contraindications, dosing adjustments over time and around procedures, drug monitoring and reversal strategies, and with communications and poor adherence by patients [7–9]. Furthermore, the direct oral anticoagulants, each with different dosage regimens based on indication and no widely available test to measure the anticoagulant effect, have increased opportunities for medication errors, while greatly increasing drug costs [2, 10, 11].

Anticoagulants are a high priority drug family for improved medication management because of (a) established benefits to reduce the risk for stroke due to atrial fibrillation by approximately 70%, the risk for recurrent venous thromboembolism by more than 90%, and the risk of death by approximately 25%; (b) widespread utilization with more than 12% of people >85 years of age taking OACs and more than 7 million prescriptions dispensed annually in Canada; and (c) ongoing under-prescribing of OACs for eligible patients, over-prescribing of reduced doses off-label, and use of inferior treatments such as aspirin [12–15].

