### Intervention

Figure 1 shows the study flow diagram including time and activities for both groups (see Additional file 1).

The Intervention Arm includes the following:Interdisciplinary intervention led by a clinical pharmacologist who is a leader in evidence-based prescribing—includes a detailed discharge medication reconciliation and management plan focussed on oral anticoagulants at hospital discharge; a circle of care handover and coordination with patient, hospital team, and community providers; three scheduled early post-discharge virtual medication check-up visits at 24 h, 1 week, and 1 month with triage of any problems. Medication reconciliation reviews hospital-administered medications compared to pre-admission medications [35]. Medication management is the more complex task of assessing and revising medications in light of the individual patient’s diagnoses, current symptoms and signs, risk factors, allergies and intolerances, other medications, and goals. In this study, all medications will be reviewed with a focus on OAC choice, dosage, indication, duration, potential drug interactions, patient risk factors for thromboembolism versus bleeding, drug insurance, adherence challenges, and health literacy. A study pharmacist with additional training will complete the detailed medication reconciliation then confer with the clinical pharmacologist who will lead the medication management including meeting with the patient and making prescription changes.Hand-overs to the community care team including the main patient caregiver (if applicable), family physician, medical specialist(s), and community pharmacist, using a templated consult summary note which includes a patient profile, details of recent hospitalization, discharge medications, an OAC monitoring checklist, circle of care and upcoming appointments, and recommendations. Figure 2 shows an example consult note (see Additional file 2)*.* The monitoring is based on (a) best evidence (updated guidelines and dedicated evidence review using the CLOT repository of CanVECTOR and McMaster’s Health Information Research Unit), and decision aid content for patients and their families to assist in anticoagulant knowledge and adherence; (b) best practices regarding discharge medication management, virtual care, scalable coordination of care with clear accountability, communication, and teletriage where situations require medical intervention [5, 16, 19, 36–40]. All consult notes are reviewed in detail with the Clinical Pharmacologist.“Virtual visits” (secure video calls from within our electronic medical record (EMR) or phone visits where video is not possible) by the study pharmacist at three follow-up time points—24 h post-discharge to ensure the discharge prescription medications were obtained and understood, review the OAC monitoring checklist, review other medications, and solicit concerns; and at 1 week and 1 month to ensure medication adherence, review the OAC monitoring checklist and other medications, and solicit concerns. After each follow-up visit, a summary consult note will be sent to all circle of care providers, and any clinical events or serious concerns will be addressed by the Clinical Pharmacologist or directed to patient’s family physician via phone call or direct email. Each follow-up visit with intervention patients will be recorded and tracked to ensure adherence to protocols.Teletriage—The patients have the study pharmacist’s contact information and can phone for assistance at any time. The study pharmacist is in constant communication with a Clinical Pharmacologist investigator for guidance. An expert thrombosis specialist will be available on call as needed.

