
Control Arm: Patients allocated to the control group will receive usual care, plus the URL to Thrombosis Canada website. Usual care in the participating sites includes OAC management by family doctors except for new thromboembolic events which will be followed short term by thromboembolism or hematology specialists, complicated atrial fibrillation which will have cardiology involved temporarily, and a small proportion of warfarin management which is provided in an anticoagulation clinic. This choice of the control group is the most relevant for generalizability to both academic and community practices.

For both arms, there are no restrictions placed on concomitant medical intervention or treatments, as this is a pragmatic randomized trial.

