### Outcomes

Study outcomes, their measurement methods, timing, and analysis are presented in detail in Table 1 and Table 2 and include the following:Primary outcomes, which are study feasibility outcomes, include recruitment and retention rates, and estimated resources required per patient to complete the main trial. Feasibility will be achieved if we can recruit at least 30% of those eligible, retain 90% of those recruited, and spend no more than $1500 per patient running the trial. Secondary feasibility outcomes include barriers and facilitators to success of the primary outcomes, in terms of process and management issues. These will be used to determine whether a large definitive research study is likely to be feasible, taking into account the practical aspects of managing and funding the project [41, 42].Secondary clinical outcomes include the following:The Adverse Anticoagulant Safety Events composite (AASE) which is any of thromboembolic events or clinically relevant bleeding or death. Thromboembolic events include objectively verified ischemic stroke, systemic embolism, pulmonary embolism, or DVT. Clinically relevant bleeds in this study is defined as bleeding that causes death, hospitalization, or emergency department visits.Coordination and Continuity of Care: Adapted from Health Quality Ontario’s draft guidance and a Rand instrument, the Coordination and Continuity of Care Questionnaire is designed to measure the quality of the transitional and follow-up care [5, 43, 44].Patient Quality of Life: The EQ-5D-5L is the 5-level classification system of the EQ-5D, a measure of health status from the EuroQol group [45]. Using EQ-5D-5L, respondents are asked a short series of questions about mobility, self-care, usual activities, pain discomfort, and anxiety/depression, as well as a summary visual analogue scale. This scale, which provides utility measurements, has been well validated for the Canadian population [45–47].Patient Knowledge of OAC Management: Insufficient patient knowledge about OAC may predict poor medication adherence and inadequate anticoagulation control [48]. The COACHeD OAC Knowledge Questionnaire tests knowledge of the therapeutic objective, process of use, safety, and maintenance of the medications [44].Satisfaction with Care: Satisfaction reported by patients and by key health professionals is one of the recommended outcomes to report in medical research, as it may influence adherence [49, 50]. This outcome will be assessed by the Patient/Caregiver Study Satisfaction Survey and by the Provider Study Satisfaction Survey [44].Medication Problems: We will be assessing problems with appropriateness, with medication errors characterized using the National Coordinating Council for Medication Error Reporting and Prevention (NCC-MERP) scale and with medication adherence and attitudes as measured by COMPETE Medication Problems Questionnaire [51, 52].Resource utilization: This is a key outcome to determine cost-effectiveness and cost-utility which then determines whether health care systems might pay for this type of care [53, 54]. We will be measuring all types of health care utilization by patients [43, 46, 54].

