	Individual Clinical Events: a) Bleeding events (clinically relevant), b) Thromboembolic events (all); c) Deaths; d) Hospitalizations or ED visits	Continuous	Intervention will have lower event rates than control	Event rate counts from end-study interviews	*T* tests

**Table 2 Tab2:** COACHeD schedule of events

Assessment	Enrolment		Study in-progress			Study end
	Baseline	Hospital discharge	24h	1Week	1 month	3 months
Eligibility screen	A					
COACHeD Brief Assessment of Capacity to Consent	B					
Informed consent	1/C					
Coordination Continuity of Care Questionnaire (CCCQ)	I/C					I/C
EQ-5D-5L v10-Canada	1/C					I/C
OAC knowledge test	I/C					I/C
Randomization and allocation	I/C					
Discharge medication reconciliation and management, circle of care communication and coordination		I				
Virtual Visit Call #1			I			
Virtual Visit Call #2				I		
Virtual Visit Call #3					I	
Adverse anticoagulant safety events (AASE)						I/C
AASE individual components						I/C
Patient/Caregiver Satisfaction Questionnaire						I/C
Provider Satisfaction Questionnaire						I/C
Health Resource Utilization Questionnaire						I/C
Medication-related problems						I/C

*A*, all potentially eligible patients; *B*, all eligible and interested patients; *I*, intervention patient; *C*, control patient; *I/C*, both groups

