### Statistical analyses

The reporting of the results of this trial will follow the CONSORT extension to pilot trials [41]. We will use descriptive statistics for presentation of baseline variables and adequacy of follow-up. Feasibility analysis including recruitment rate (≥30% is considered success), participant retention rate (≥90% to end of study is considered success), study resource utilization required (CAD $1500 per patient recruited and completing the study is considered a threshold), management assessment, and scientific assessment will be descriptive.

Analysis will use intention-to-treat methods with censoring only if the patient dies or drops out of the study with refusal of negotiated further assessments. A sensitivity analysis of the subgroup of patients who received all 3 planned follow-up intervention calls and completed the end-study data collection (per protocol analysis) will be carried out. Research staff and statisticians will review outcome data and analysis blinded to group identification.

The primary clinical endpoint will be the incidence of adjudicated AASE during the follow-up period, using proportions, and chi-square testing. Secondary endpoint analyses of the coordination and continuity of care, patient quality of life, OAC management knowledge satisfaction with care (providers & patients), and resource utilization will be analyzed using *t* tests. The incidence of the adjudicated individual clinical events (clinically relevant bleeding events, thromboembolic events, all-cause hospitalizations, and emergency department visits) will be analyzed using the methods described above for AASE. Public unit costs from Ontario will be used to cost healthcare resource utilization collected as part of the trial. Using an area under the curve approach, quality-adjusted life years (QALYs) will be determined by weighting the EQ-5D-5L health utility scores by time spent in health state. Costs and outcomes (i.e., QALYs, AASE) between the interventions will be compared from a public payer perspective. Given the short follow-up, a low risk of the trial and pilot design, no interim analysis or imputation for missing data is planned. All analyses will be performed using SAS V9.4 software (SAS Institute Inc., Cary, NC, USA).

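### The per-protocol set as written admits no control patients, and if controls enter under a looser rule it selects the intervention arm alone on first-month survival and contact

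*Protocol article*

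**What the plan says.** The Statistical analyses section sets the main analysis as follows: "Analysis will use intention-to-treat methods with censoring only if the patient dies or drops out of the study with refusal of negotiated further assessments". It then adds one sensitivity analysis, of the "subgroup of patients who received all 3 planned follow-up intervention calls and completed the end-study data collection (per protocol analysis". No membership rule for controls is given.

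The calls belong to the intervention, described as "three scheduled early post-discharge virtual medication check-up visits at 24 h, 1 week, and 1 month". In Table 2 the rows from "Virtual Visit Call #1" to the third call carry the code for the intervention group only. For the other arm, the Intervention section says: "Patients allocated to the control group will receive usual care, plus the URL to Thrombosis Canada website".

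The composite that the clinical comparison rests on, AASE, is defined under Outcomes as "any of thromboembolic events or clinically relevant bleeding or death". On timing, Background and rationale reports that the group's earlier study of thromboembolic and hemorrhagic events "found rates to be approximately 2 to 3 times higher in the first month compared to later".

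**The concern.** There are two linked problems.

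First, the rule cannot be met by anyone in the control arm, so the stated subgroup supports no comparison between arms.

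Second, to run the analysis at all, someone must admit controls on a different rule. Intervention patients would then have to be alive and contactable at 24 hours, 1 week and 1 month, and controls would not. That window is the one the protocol describes as having the highest event rates. An intervention patient who dies before the 1-month call must leave the set. One who dies later also leaves it unless a caregiver completes the end-of-study assessment. Both are AASE events.

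At stake is how the only sensitivity analysis named in the article is read. The abstract says that the pilot is to judge feasibility and merit for a full trial. A difference produced by selection could be taken as support for merit.

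**Working it through.** **The plan's own figure.** The documents give no AASE rate, effect size or power. The only computed figure is the sample of 59: ln(0.05)/ln(0.95) = 58.40, rounded up to 59, with 1 − 0.95^59 = 0.9515 and 1 − 0.95^58 = 0.9490. It reproduces. It matters here only as a scale of about 30 per arm.

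**Literal reading.** Controls scheduled for calls: none (Table 2). Controls who can have received all three: 0. No risk ratio can be formed.

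**If controls are admitted, under no treatment effect.** Inputs:
- r = first-month rate as a multiple of the later rate, 2 to 3 (Background and rationale). The source figure concerns thromboembolic and hemorrhagic events; applying it to all AASE is an assumption.
- R = 3-month AASE risk, equal in both arms; f = share of AASE that are deaths; q = chance that a non-fatal first-month AASE causes a missed call. All three are assumptions: R 5% to 20%, f 20% to 40%, q 0 to 0.5.
- Deaths are taken as not completing the end-of-study assessment, except where stated.

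Formulas:
- Share of 3-month events in month 1: s = r/(r + 2), so 2/4 = 50% or 3/5 = 60%.
- Non-fatal risk: N = R(1 − f).
- Per-protocol intervention proportion: N(1 − sq) / [N(1 − sq) + (1 − R)].
- All controls: R. Completing controls: N / (N + 1 − R).

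| Setting (R = 10%) | Per-protocol intervention | RR vs all controls (10.0%) | RR vs completing controls |
|---|---|---|---|
| f = 20%, q = 0 | 0.08/(0.08 + 0.90) = 8.2% | 0.82 | 1.00 (8.2%) |
| f = 20%, r = 2, q = 0.25 | 0.07/(0.07 + 0.90) = 7.2% | 0.72 | 0.88 (8.2%) |
| f = 40%, r = 3, q = 0.5 | 0.042/(0.042 + 0.90) = 4.5% | 0.45 | 0.71 (6.25%) |

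Over the whole assumed grid the ratio against all controls runs from 0.83 to 0.43. Against completing controls it is 1.00 at q = 0, 0.85 to 0.89 at q = 0.25, and 0.71 to 0.78 at q = 0.5.

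**If caregivers complete the assessment for every death.** Only first-month deaths in the intervention arm then drop out. With R = 10%, f = 20%, q = 0 and deaths following the same time pattern: r = 2 gives (0.10 − 0.01)/(1 − 0.01) = 9.1%, RR 0.91; r = 3 gives (0.10 − 0.012)/(1 − 0.012) = 8.9%, RR 0.89. All controls then count as completers, so the ratio is the same against either control group.

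**If well patients skip calls.** Take R = 10%, f = 20%, q = 0, and let 20% of event-free intervention patients miss a call: 0.08/(0.08 + 0.90 × 0.80) = 0.08/0.80 = 10.0%. The ratio is 1.00 against all controls and 0.100/0.0816 = about 1.23 against completing controls.

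**At the pilot's size.** In 20,000 simulated trials with 30 per arm, an uncorrected chi-square test falsely favoured the intervention (nominal 2.5%) in 4.5% of runs in the first row of the table against all controls, and in 2.4% against completing controls. At R = 20%, r = 3, f = 40%, q = 0.5 the figures were 19.4% and 5.9%. In patients, the first-row shift is small: (0.100 − 0.082) × 30 is about half a patient.

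**The case against.** A reader might infer that this set favours the intervention whenever there is no effect, and that it removes all deaths and all early events. The documents do not support that, for four reasons.

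- Read literally, the set has no controls and so favours neither arm. The bias needs a control rule that the text does not state.
- A non-fatal early event removes a patient only if it leads to a missed call or missing end-of-study data. Calls may be by video or phone, and someone readmitted or seen in an emergency department can still take one.
- Data collection methods allows interviews with caregivers, so completion after a death later than month 1 is not ruled out.
- The direction is not fixed, as the case of well patients skipping calls shows.

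It can also be said that an article leaves detail to the full protocol, that this is a supportive analysis of a secondary outcome, and that for the 3-month questionnaires completion cannot be avoided.

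Most of this stands, and it limits the size and certainty of the point. It does not rescue the rule. An unstated control definition alone would be omitted detail, but the definition that is stated excludes one whole arm, and it necessarily drops intervention patients who die before the 1-month call.

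**Conclusion.** The per-protocol definition is wrong as stated. It yields no between-arm comparison, and any version that admits controls on a looser rule conditions one arm only on survival and contact after randomization.

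With no true effect, the result can then favour the intervention: a risk ratio of about 0.82 against all controls from deaths alone (10% AASE risk, 20% of it deaths). It is lower if early non-fatal events cause missed calls, nearer 0.9 if caregivers complete for every death, and 1.00 or above if enough event-free patients skip calls. Where deaths fail completion in both arms and non-fatal events cause no missed calls, the bias against completing controls is nil. Every size here rests on assumed event and missed-call rates, because the protocol gives none.

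An analysis whose null value moves this much with unstated choices cannot test the robustness of the intention-to-treat result. Severity is minor to moderate: the intention-to-treat analysis remains the main one, and the recruitment, retention and cost criteria do not depend on this set.

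**What to change.** For AASE, do not require end-of-study completion from patients who died or already had an adjudicated AASE, and count deaths as events. Then choose one of two routes:

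- (a) Compare the arms from a 1-month landmark with the same entry condition in both arms, and state that this estimates only risk after month 1.
- (b) Report completion of the three calls as a descriptive adherence summary of the intervention arm, with no comparison.

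Label any per-protocol comparison exploratory, since call receipt has no control counterpart. A rule that ends the call requirement at a patient's first AASE and keeps all controls should be avoided: early-event patients would qualify more easily than event-free ones, which is a new asymmetry. The completion condition may stay for the 3-month questionnaires.

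The cost is about one sentence in Statistical analyses. No new data are needed, because the follow-up visits are already recorded and tracked.

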### Data monitoring

Since this trial does not involve any investigational product or procedure, and uses the main anticoagulant safety events and medication safety as outcome events, a formal Data Safety Monitoring Board is not required. Any serious adverse event will be reviewed by our Trial Steering Committee (TSC) within a week of detection, to discern any attribution to our procedures. If found to be due to our coordination procedures, the trial steering committee will recommend whether modifications are indicated. The TSC will be composed of individuals with expertise in clinical trials, chaired by the lead statistician, include the PI, the operational statistician plus a methodologist independent of the study team. Similarly, since this is a short pilot pragmatic RCT where no harm is expected and adjustment of trial procedures may be necessary for feasibility, no formal external auditing of trial conduct is planned. There is no requirement for additional ancillary and post-trial care for those who might come to harm while in the trial, as usual medical care which covers this eventuality is already in place.

### Trial management

The trial Principal Investigator will be responsible for communicating any changes to the study, new information, or unanticipated events to the REB, to the sponsor, and to Local Principal Investigators (LPI). The LPI (also called Site Investigator) is responsible for supervising any individual or party to whom they have delegated tasks at the trial site. A Trial Management Group (TMG) will be responsible for the day-to-day management of the trial and will include at a minimum the trial PI, the local PIs, and the trial Research Coordinator. The group will closely review all aspects of the conduct and progress of the trial, ensuring that there is a forum for identifying and addressing issues. Particular attention will be paid to progress towards trial milestones, adherence to the protocol and good research practices. Meetings will be minuted and retained in the study REDCap database.

